### Consent and enrollment

The CHW notifies his/her health area data collector about the identification of the eligible child. On Day 7 after identification, the data collector and the CHW jointly visit the child’s household to formally conduct an oral informed consent process, enroll the child, conduct the day 7 assessment, and record outcome and covariate data.

Upon first arriving at the home, the data collector reads aloud a consent script explaining the study, the CHW assessment procedures, and data collection activities, and answers any questions the caregiver might ask. If the caregiver verbally agrees to study participation, the data collector records vital status, axillary temperature, respiratory rate, and MUAC, and the CHW follows the iCCM algorithm to assess the child and query the caregiver about the child’s signs. Specifically, the CHW asks the mother if the child has cough, fever, diarrhea or any problem, and assesses the child for danger signs (unable to drink or breastfeed, vomiting everything, convulsions, loss of consciousness, chest-in drawing), warning signs (low MUAC, persistent illness, difficulty breathing/wheezing, signs of possible anemia), signs of malnutrition (visible signs of wasting, edema of lower limbs), and other signs (diarrhea, with or without blood in stool, generalized rash, and mother’s report of fever). In the event of reported fever by the caregiver, the CHW will check for malaria using a mRDT (and provide treatment, as necessary); if cough is reported by the caregiver the CHW will count the child’s respiratory rate to assess pneumonia. The data collector records all information from the assessment and also administers a structured questionnaire to elicit information on infant, maternal/paternal, and household variables, as well as on care-seeking behaviors.

Finally, information about the child’s initial visit to the CHW and any interim visits to the CHW (i.e. between identification of eligibility and the Day 7 assessment visit) is extracted by the data collector from the CHWs iCCM records. This extraction process provides an additional opportunity for the data collector to confirm that the initial eligibility assessment by the CHW was correctly done; permission to extract this information from the iCCM records is included in the consent process described above.

### Follow up of sick children

If the caregiver reports that the child has a fever, or if the CHW determines that the child has any danger signs, or has to be treated for malaria, diarrhea, or pneumonia during the follow up visit on Day 7 (i.e. child meets the primary outcome definition), an additional follow up visit is planned on Day 14 for the child. At this second home visit, the CHW and data collector again conduct the same health assessment as described above and the outcome of the visit is recorded. As before, if a child at a Day 14 visit is determined to have fever, any danger sign, or one of the three CHW-treatable illnesses, the appropriate treatment and/or or referral advice is provided, and a third visit is scheduled for Day 28. Thus, sick children are followed up at Day 14, and Day 28, if necessary. The vital status (alive/died) of all enrolled children is recorded by the data collector 30 days after initial enrollment, regardless of number of follow up visits conducted.

### Quality control and supervision

In order to ensure that all eligible children are correctly identified, data collectors check the registers of CHWs in the health area where they work on a weekly basis.

Quarterly meetings are organized for all data collectors and research support staff to provide feedback based on the data collected, to address challenges experienced by the data collectors in the field and to identify best practices. In addition, each data collector receives a quarterly individual supervision visit in the health area where (s)he works. During this visit, the Research Manager accompanies the data collector on a Day 7 visit to observe and evaluate the data collector while at work and to provide coaching and feedback in order to strengthen the data collector’s capacities. In addition, the Research Manager conducts spot checks of CHW registers working in the data collector’s health area during the individual supervision visit to ensure that all eligible children are identified by the CHWs and data collectors.

### Data management

All data are collected on paper forms by data collectors. Data collectors use an extraction form to transfer information from the CHWs iCCM records (i.e. register, individual sick child form) for the enrolled child. Other forms are filled out during household visits with enrolled children on Day 7, and, if necessary, on Day 14 and Day 28. Each enrolled child receives a unique six-digit code (“case id”) in order to ensure a linked chain of forms, as well as to protect the child’s and caregiver’s identity. Forms are checked for accuracy and completeness by the Research Manager and a Data Officer prior to data entry in Kalemie. All data forms are double-entered into a secure online database (REDCap) [12] using customized data entry screens, with built-in validation checks. De-identified analytic files are constructed from the raw REDCap database files.

### Analysis

All children enrolled and providing available data from the follow-up visit on Day 7 will be included in the analysis. First, we will present descriptive information on the recruitment, enrollment, and follow up of children with uncomplicated fever using a participant flowchart (Fig. 1). We will then assess characteristics of enrolled children to determine the extent to which our randomization procedure at the health area level achieved balance across the study arms; these characteristics will include infant, maternal/paternal, household, and socio-economic variables. Variables that are imbalanced will be noted for possible inclusion in a subsequent adjusted analysis.

**Fig. 1 Fig1:**
[figure not shown]
Trial design flowchart

The next stage of the analysis will focus on the primary outcome, failure at Day 7 visit, which is defined as fever, diarrhea, pneumonia or decline of health status (e.g. hospitalization, presenting danger signs, or death). In each study arm, the failure proportion will be estimated as the number of children that “failed”, and the non-inferiority of the two approaches to follow up advice (“universal” vs “conditional”) will be assessed by comparing these proportions across the two groups. The difference in these rates (proportion of children that failed in the conditional follow-up group minus proportion of children that failed in the universal follow-up group) along with a one-sided 95% confidence interval will be estimated. If the upper bound of this confidence interval is less than 0.04, we will reject the null hypothesis and conclude that the conditional follow-up approach is not inferior to the universal follow-up approach. If we have noted variables that are imbalanced across the allocation groups, we will conduct adjusted analyses of the difference in proportion using multivariate binomial regression models with an identity link function. A priori specified sub-analyses will include those where the women and CHWs both report providing the per-protocol advice, those where fever is detected based on axillary temperature (rather than caregiver’s report), and stratified by number of days of fever reported (>2 vs < =2). Secondary outcomes described previously will be examined using descriptive analytic approaches.

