### Randomization

The unit of randomization in this trial is the health area (*n* = 28), and CHWs working within a particular health area are thus allocated to the same group (either “universal” or “conditional” follow-up advice given to caretakers of eligible children); all children enrolled by CHWs within a health area constitute the study cluster. Allocation to the “universal” versus “conditional” arm was done via restricted randomization whereby units were balanced on zone and health area estimates of 1) population size, 2) prior 6-month likelihood of mRDT-negative febrile children (number of children mRDT negative/under-five population), and 3) geographic distance from CHW to zonal health center. Of all possible randomization sequences (*n* = ~40.1 million, generated using STATA version 13.1), 43,504 sequences were balanced on zone ***and*** had ratios of the above three indicators between 1/1.05 and 1.05. After confirming the validity of the restriction procedure (approximately equal probability of any two units being assigned to the same or different arms), one of these sequences in the restricted subset was selected at random. It was not possible to mask the clustered allocation from participants, CHWs, or data collectors).

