### Sample size

To calculate sample size, we set the outcome rate in the “universal” follow-up group to 5%, and assumed that the (true) corresponding outcome rate in the “conditional” follow up group is no more than 6%. For the purposes of concluding that the “conditional” follow up is non-inferior to the “universal” follow up approach, using the simple approach outlined by Blackwelder [10] and extending the methods of Hayes and Bennett [11], we first estimated the coefficient of variation (k) of the true failure rate across our available health areas; we conservatively estimated that k is 0.35, implying that the true cluster-specific failure rates vary between 1.5 and 8.5% (i.e. 5%*(1 ± 2 k)). Next, utilizing data from the first six months of 2015, aggregated from monthly reports from CHWs working in Kalemie and Nyemba health zones, we anticipated that approximately 493 negative mRDT cases would occur per month over 28 health areas. We estimated that about 70% of these mRDT negative cases would be eligible (i.e. excluding those cases with danger signs or other CHW treatable conditions [pneumonia, diarrhea]). Given the above assumptions, and desiring 12 complete months of enrollment, the estimated average cluster size over that anticipated timeframe is equal to (70%*493*12)/28 = 148. Assuming that about 10% of the eligible children will not participate or will be lost to follow up (reducing this yield to 148*.09 = 133, the total number of health areas required to detect (with 80% power) non-inferiority of the “conditional” follow up approach given the above parameters was 24, (12 per group). Rather than exclude just 4 of our available 28 health areas, we decided to include all 28, increasing the number of clusters to 14 per group (this increased our estimated power to 86.8%), and leading to an initial estimated final enrollment of 3730 children. After approximately 6 months of actual study enrollment, however, our actual observed per-cluster yield had increased to 152, leading to a revised estimate of the total enrollment; by the completion of the enrollment period, we will enroll approximately 4270, or 2135 children per group.

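### The Analysis section names no allowance for the 28 randomized health areas; taken literally, the one-sided 95% bound tested against the 4-point margin would be too narrow

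*Protocol article*

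**What the plan says.** The Randomization section of the protocol article is explicit about the unit: "The unit of randomization in this trial is the health area", and "all children enrolled by CHWs within a health area constitute the study cluster".

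The Sample size section carries this through. It extends a cluster-trial formula to non-inferiority, and on between-area variation it says "we conservatively estimated that k is 0.35". It finds that 12 health areas per group are needed, then uses all that are available, "increasing the number of clusters to 14 per group", for a stated power of 86.8%.

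The Analysis section (the text after Fig. 1) sets the failure proportion in each arm from the number of children who failed. Non-inferiority "will be assessed by comparing these proportions across the two groups". The difference gets a one-sided 95% interval, and non-inferiority is concluded if the upper bound is below 0.04. For imbalanced covariates, "we will conduct adjusted analyses of the difference in proportion using multivariate binomial regression models with an identity link function". Three sub-analyses follow. In the whole section the health area appears only as the level of randomization, when baseline balance is checked. No cluster term, robust variance, random effect, cluster-level summary or cluster degrees of freedom is mentioned for the interval or for the regression.

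**The concern.** The design and the described analysis appear to rest on different variances. The sample size adds a between-area component to the binomial variance. The analysis text, read at face value, uses the binomial component alone and so treats some 4,270 children as the independent units, although only 28 units were randomized.

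The trial's conclusion depends on one number, the upper bound compared with 4 points. Omitting between-area variance lowers that bound. The error therefore runs one way: a conditional policy that is truly 4 points worse would be declared non-inferior too often. The article intends the result to support simplifying follow-up guidance in the DRC and elsewhere.

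**Working it through.** **Inputs, all from the protocol article.** Failure is 5% in the universal arm and 6% in the conditional arm under the design alternative (Sample size). The margin is 4 points, so the null boundary is 5% against 9% (Aims). Alpha is one-sided 0.05 (Aims, Analysis). k = 0.35, with 14 clusters per arm. Cluster size m is 133 as planned (148 × 0.9; the printed .09 is evidently a misprint) and 152 as revised (Sample size).

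**1. Reproduce the plan's own figures.** Clusters per group:

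c = 1 + (z₀.₉₅ + z₀.₈₀)² × {[p₀(1−p₀) + p₁(1−p₁)]/m + k²(p₀² + p₁²)} / (0.04 − 0.01)²

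With p₀ = 0.05, p₁ = 0.06 and m = 133:
- binomial part: (0.0475 + 0.0564)/133 = 0.000781
- between-cluster part: 0.1225 × 0.0061 = 0.000747
- c = 1 + 6.183 × 0.001528/0.0009 = 11.5, so 12 per group, as stated.

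Power with 14 per group (c − 1 = 13): SE = √(0.001528/13) = 0.01084, and Φ(0.03/0.01084 − 1.645) = 86.9%, against 86.8% stated.

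Without the between-cluster part, c = 1 + 6.183 × 0.000781/0.0009 = 6.4, so 7 per group. The stated 12 therefore depends on the variance component that the Analysis section does not mention.

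**2. Error of an unadjusted bound at the margin (5% against 9%).**

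Design effect DE = 1 + k²(p₀² + p₁²) / {[p₀(1−p₀) + p₁(1−p₁)]/m}; actual one-sided error = 1 − Φ(1.645/√DE).

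The between-cluster part is 0.1225 × 0.0106 = 0.001299. The binomial part is 0.1294/m.

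| m | DE | unadjusted SE (points) | true SE (points) | actual error |
|---|---|---|---|---|
| 133 | 2.33 | 0.83 | 1.27 | 14.1% |
| 152 | 2.53 | 0.78 | 1.24 | 15.0% |

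A beta-binomial simulation with 14 clusters per arm and 50,000 runs gives 14.4% and 15.4%.

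**3. Sensitivity of that error.**
- Between-cluster SD held at 0.35 × 5 = 1.75 points in both arms, rather than rising to 0.35 × 9 = 3.15 points at 9%: 9.9% (m = 133) and 10.5% (m = 152).
- k = 0.20: 8.5% and 9.0%.
- k = 0.10: 5.9% and 6.0%.
- k = 0.50, m = 152: DE = 1 + 0.25 × 0.0106/0.000851 = 4.11; error about 21%.
- k = 0.35 with unequal cluster sizes (assumed coefficient of variation 0.5), by simulation: 15.9% and 17.2%.

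**4. What a cluster-level analysis would give.** A t analysis of the health-area proportions on 28 − 2 = 26 df has a simulated error of 5.7% (m = 133) and 5.9% (m = 152) at k = 0.35. Its power at 5% against 6% is 86.9% and 88.9%.

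**5. An illustration where the conclusion changes.** Suppose 5% and 7.5% are observed, with m = 152 and k = 0.35.
- Unadjusted: SE = √(0.116875/152/14) = 0.74 points; upper bound 2.5 + 1.645 × 0.74 = 3.7 points, below the margin.
- Cluster-level: SE = √[(0.000769 + 0.1225 × 0.008125)/14] = 1.12 points; upper bound 2.5 + 1.706 × 1.12 = 4.4 points, above the margin.

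**The case against.** A reader might infer that the plan prescribes an analysis of independent children, so that false non-inferiority is in fact about three times as likely as stated. The document does not support that, for three reasons.

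First, the Analysis section is silent on the variance; it does not state independence. A difference of pooled arm proportions is a legitimate point estimate in a cluster trial when paired with a cluster-robust variance. A binomial family with identity link can be fitted by GEE or with robust standard errors. The title, Randomization and Sample size sections all show that the authors know the trial is clustered.

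Second, this is a condensed article. A full protocol or SAP that is not shown may specify the variance method, and details such as degrees of freedom are commonly left there.

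Third, the factor of three is not fixed. It needs an unadjusted variance, k = 0.35 (which the article calls conservative), and the same k at a 9% failure rate. Restricted randomization on zone, population, prior mRDT-negative likelihood and distance may also lower the relevant between-area variance.

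All three stand as limits on the claim, and the size must be stated conditionally. They do not remove the point. The section does not defer the primary analysis: it fixes the estimator, interval level, decision rule, regression family, link and sub-analyses, and in all of that nothing reflects the randomized unit. At every non-zero k examined, the unadjusted error exceeds 5%, so the direction does not depend on the exact value.

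**Conclusion.** The point holds in conditional form. The analysis as described omits any allowance for the 28 health areas on which the randomization and sample size rest. If it were carried out literally, the bound that decides the trial would be too narrow. On the design's own k and cluster sizes, the one-sided error at the margin would be about 14-15% instead of 5%. Under the weaker assumptions it would be about 10% (constant SD of 1.75 points) or about 9% (k = 0.20), and with k = 0.50 about 21%. These figures assume 14 clusters per arm, failure of 5% against 9% and, apart from the simulation with unequal sizes, equal cluster sizes. The document does not show that such an analysis is intended. Because the text at issue sets the pass/fail criterion, it should still be corrected and not left to inference.

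**What to change.** State in the Analysis section that the primary difference and its one-sided 95% upper bound account for the 28 health areas, and that the adjusted model and the sub-analyses do the same. Either of two methods would serve:
- a cluster-level analysis of health-area failure proportions with a t reference on 26 df (fewer if adjusted); or
- GEE or binomial identity-link regression with a small-sample-corrected cluster-robust variance.

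If a SAP already specifies such a method, name it in the Analysis section and refer to the SAP.

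The cost is a change of wording and a wider interval than an unadjusted one. The sample size already assumes that width: power stays at about 87-89% under the plan's assumptions, with no added clusters or children.

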### Monitoring

An 3-person Data Monitoring Committee was formed to periodically receive from investigators updates on enrollment progress and numbers of deaths and hospitalizations. As the invention consisted of a change in follow-up schedule only, and all participants received usual care (i.e. followed iCCM guidelines) from CHWs at follow up visits, there was no formal interim analyses conducted for safety, efficacy, or futility.

## Discussion

This study, expected to be completed by the end of 2016, is a cluster-randomized, community-based non-inferiority trial evaluating conditional follow up versus a universal follow up of children who present uncomplicated fever and seek care at a CHW site. The results from this study will provide an evaluation of the clinical deterioration (“failure”) of children between 2 and 59 months of age that presented with an uncomplicated fever to a CHW and subsequently received universal versus conditional follow up. Furthermore, the results from this study will provide information regarding the clinical presentation, care-seeking patterns, and outcomes among children that are classified as “failed” at Day 7, the frequency of scheduled and spontaneous visits among all children, hospitalization and death rates among all children, and longer-term outcomes (based on data collected during Day 14 and Day 28 household visits) of children that were classified as “failed” at Day 7.

If the conditional follow up of children with uncomplicated fever is shown to be non-inferior to the current WHO iCCM protocol prescribing universal follow up of children with uncomplicated fever by CHWs, this will suggest that current guidelines can be simplified, having significant implications for community-based case management of uncomplicated fever in the DRC, and in many other settings. Simplification of the current iCCM algorithm by recommending a conditional follow up for children with uncomplicated fever will reduce unnecessary follow-up visits and reduce the burden on both CHWs and caregivers. Results will be interpreted in conjunction with a similarly designed trial testing the same hypothesis being conducted concurrently in Ethiopia.

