## Methods

### Aims

The primary aim of this study is to determine if the likelihood of clinical deterioration (“failure”) among children between 2–59 months of age in Tanganyika Province, DRC that present with an uncomplicated fever to CHWs is similar between those advised universally to be followed up on Day 3 and those advised for follow up only if illness does not resolve. At seven days post-enrollment, children are considered as “failed” if they present with persistent fever, persistent illness, or decline of health status (e.g. hospitalization, presenting danger signs, or death). We hypothesize that the proportion of children that meet this primary outcome determination under current guidelines (“universal”) is 5% and that the true rate of failure in the condition under study (“conditional”) is 6%. The null hypothesis is that the conditional follow-up approach is inferior and that children in this group will yield a failure rate at least 4% higher than that of the universal follow-up group. Conditional follow-up will be considered non-inferior to universal follow up if the upper bound of a one-sided 95% confidence interval around the absolute difference in outcome rate (conditional follow up minus universal follow up) does not exceed 4%.

Secondary aims of the study include describing the clinical presentation, care-seeking patterns, and outcomes among children that are classified as “failed” at Day 7, estimating the frequency of scheduled and spontaneous visits among all children, hospitalization and death rates among all children, and longer-term outcomes (based on data collected during Day 14 and Day 28 house visits) of children that were classified as “failed” at Day 7. In addition, a qualitative portion of the study with a limited sample size will look at CHWs’ and caretakers’ perceptions of the conditional vs. universal follow-up message.

Enrollment for this study was initiated in October 2015 and will be completed by the end of 2016. The study is a collaboration between the International Rescue Committee (IRC) and the Johns Hopkins Bloomberg School of Public Health.

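### A positive Day 7 result cannot by itself show that fewer Day 3 visits are safe or that visits fall; the between-arm visit difference needs an estimate with an interval, not description alone

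*Protocol article*

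**What the plan says.** All references are to the protocol article.

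- **Intervention.** Under Eligibility and intervention, what differs by arm is the message: every caregiver is told to return on Day 3, or is told to return only if the child has not improved. Attendance itself is not assigned.
- **Decision rule.** Aims uses the "upper bound of a one-sided 95% confidence interval around the absolute difference in outcome rate" (conditional minus universal), with a 4-point margin. Analysis repeats it: "If the upper bound of this confidence interval is less than 0.04, we will reject the null hypothesis". Non-inferiority of the conditional approach is then declared.
- **Visits.** Aims lists the frequency of scheduled and spontaneous visits among all children as a secondary aim. Consent and enrollment provides the data: "any interim visits to the CHW (i.e. between identification of eligibility and the Day 7 assessment visit) is extracted by the data collector". The source is the register and forms kept by each CHW. Analysis fixes the handling: "Secondary outcomes described previously will be examined using descriptive analytic approaches".
- **Adherence.** The only adherence-type analysis is by message: "A priori specified sub-analyses will include those where the women and CHWs both report providing the per-protocol advice".
- **Conclusions.** The Discussion speaks of children as having received one or the other form of follow-up. It says that non-inferiority would suggest the guidelines can be simplified, and then states without condition: "Simplification of the current iCCM algorithm by recommending a conditional follow up for children with uncomplicated fever will reduce unnecessary follow-up visits", together with the burden on CHWs and caregivers. The Abstract is softer: it says updated guidelines *could* reduce these pressures.

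**The concern.** Advice can change Day 7 failure mainly by changing who is seen on Day 3. If universal-arm caregivers often do not come back, or conditional-arm caregivers come back anyway, care in the two arms converges. In a non-inferiority trial, convergence favours a positive result. Incomplete attendance is plausible on the article's own account: the Background says caregivers often walk long distances to reach a CHW. The article gives no attendance figure.

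A positive result then has two readings: Day 3 visits can be omitted without a loss of 4 points or more, or Day 3 visits hardly changed. The primary analysis cannot tell them apart. Under the second reading, the benefit that motivates the trial, fewer visits, would be largely absent. Yet that benefit is the one the Discussion states as certain, and the plan gives it no between-arm estimate or interval.

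**Working it through.** **Inputs** (Aims and Sample size): universal failure 5%, conditional failure 6%, margin 0.04, one-sided 5%, k = 0.35, 14 clusters per arm, m = 133 children per cluster as planned. The later yield of about 4270 children over 28 clusters gives m = 152.5.

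**1. Reproduce the stated design.** Cluster formula based on the coefficient of variation, with a non-inferiority margin:

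v = [p0(1−p0) + p1(1−p1)]/m + k²(p0² + p1²)

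v = (0.0475 + 0.0564)/133 + 0.1225 × (0.0025 + 0.0036) = 0.000781 + 0.000747 = 0.001528

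Clusters per arm for 80% power = 1 + (1.645 + 0.842)² × 0.001528/0.03² = 11.5, so 12, as stated.

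Power with 14 per arm = Φ(0.03 × √(13/0.001528) − 1.645) = Φ(1.12) = 86.9%. The article states 86.8%, so the design is reproduced.

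**2. Chance of meeting the rule when both arms have the same failure rate p.** Now p0 = p1 = p, and the distance to the margin is 0.04.

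- p = 5%: v = 2 × 0.0475/133 + 0.1225 × 0.0050 = 0.001327; Φ(0.04 × √(13/0.001327) − 1.645) = Φ(2.31) = 99.0%.
- p = 10%: v = 2 × 0.09/133 + 0.1225 × 0.0200 = 0.003803; Φ(0.04 × √(13/0.003803) − 1.645) = Φ(0.69) = 75.6%.

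| Common failure rate | k | m | Chance that the rule is met |
|---|---|---|---|
| 5% | 0.35 | 133 | 99.0% |
| 5% | 0.35 | 152.5 | 99.3% |
| 6% | 0.35 | 133 | 96.6% |
| 10% | 0.35 | 133 | 75.6% |
| 5% | 0.25 | 133 | 99.8% |
| 5% | 0.50 | 133 | 94.6% |

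A simulation with beta-binomial clusters and a cluster-level t bound (40,000 trials per scenario, m = 133) agrees: 87.0% for 5% vs 6%, 99.0% for 5% vs 5%, and 77.0% for 10% vs 10%.

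**3. What the plan would show about separation.** Visits by arm will be tabulated, since they are a secondary aim and the data are extracted. No between-arm difference or interval is stated, and neither Discussion claim refers to the table. The per-protocol subset confirms that the message was given. It does not show whether attendance differed.

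**The case against.** The strongest reply is that the rule answers the question asked. The guideline under challenge is itself advice, advice is what is randomized, and Analysis describes the comparison as one of approaches to advice. Imperfect attendance is part of how universal advice performs, so its replacement is fairly judged against it as delivered. This stands, and the primary rule should not change.

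A reader might infer that the 99% is a false-positive rate. It is not: with 5% in both arms, declaring non-inferiority is correct. The same caution applies to partial attendance. Assume failure of 5% with the visit and 9% without it, and no attendance in the conditional arm. Simulation (m = 152) then meets the rule 6% of the time at full universal-arm attendance and 53% at 40%. At 40% the true difference between the advice policies is 4 × 0.40 = 1.6 points, inside the margin, so the 53% is not an error of a rule that compares advice. The 4-point cost and the attendance levels are also assumed, not documented.

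A reader might also want the guideline conclusion to depend on a superiority test for visits. That is not supported. Such a test would pass easily at attendance of 40% to 90% against none, so it would leave those figures unchanged and block only near-zero separation, which an interval already shows.

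Three further points carry weight. Visits will be reported, so poor separation would be visible. The quoted sentence is an expectation about a changed guideline, and the step from non-inferiority to simplification is hedged. Conditional advice may also change which children return without changing how many, so equal attendance need not mean equal care. These points limit the concern but do not remove it. The article itself specifies description only and states the fall in visits without condition, so this is not a detail merely left to an analysis plan that is not shown.

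**Conclusion.** The primary rule is a valid test of non-inferiority between two kinds of advice. A positive result does not by itself show that fewer Day 3 visits are safe, or that visits fall, because it would also be expected if attendance hardly differed: about 99% of the time at the planned 5% failure rate and k = 0.35, falling to about 76% at 10% failure. These figures assume that the advice acts mainly through the Day 3 visit, so that similar attendance means similar failure.

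The defect lies in the secondary analysis and the wording. The visit contrast is left to description, adherence is defined by the message, and the Discussion treats the reduction in visits as certain where the Abstract does not. The documents do not support a claim that the rule has an inflated error rate, nor that attendance will in fact be poor.

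**What to change.** Keep the primary rule and sample size, and make three changes.

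1. **Analysis.** Using the CHW-record data already extracted, estimate the between-arm difference in (a) the proportion of children with a CHW visit on Day 3 and (b) the number of CHW visits between the Day 1 consultation and the Day 7 assessment. Give cluster-adjusted 95% confidence intervals, for example from the 28 cluster summaries. Report both beside the primary result.
2. **Interpretation.** State that visits were reduced only if the interval shows it. Otherwise word the conclusion as non-inferiority of the advice as delivered, with the observed separation shown. Do not make the guideline conclusion depend on a superiority test.
3. **Discussion.** Replace the unconditional statement on visits and burden with wording in line with the Abstract, and refer to children whose caregivers were given each kind of advice.

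Do not add a subset defined by individual attendance. Conditional-arm children are asked to come when they are still ill, so attenders in the two arms are not comparable.

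The cost is one more cluster-level comparison and a few sentences, with no extra children, visits or data. The downside is that the visit-reduction claim may turn out weaker than now written.
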